**Study outline – Phase 1**

**Week**

0

2

14

12 week walking based exercise programme

**Key:**

Randomisation and group allocation, timetable details finalised for exercise groups

Fasting venesection, anthropomorphic measurements

and questionnaires

Exercise treadmill testing - measurement of VO2 max

**Initial screening and consent**

Potential subjects will be pre-screened by phone to assess their study eligibility ie to determine whether or not they fulfil study inclusion criteria. This pre screening will be undertaken by the research nurse or one of the named investigators. Potential subjects will then be invited to a group meeting at the Christchurch Diabetes Centre to discuss the study, including the need for exercise testing. Potential participants will be encouraged to ask questions about the study. They will be given the information and consent sheets at that meeting. Potential participants will be encouraged to discuss the study with their GP. Potential participants can then either complete the consent sheet at that meeting or, if they prefer, send it back in an s.a.e., to be countersigned by the investigator at the first baseline testing visit (see below). It is anticipated that up to 10 such group meetings will be required to enable screening of sufficient numbers of potential participants.

**Baseline Testing**

About a week prior to baseline testing, consenting subjects will be sent a four day food record and instructions about completing this, the quality of life and health and exercise history questionnaires and the facilitators and barriers to change questionnaire. They will also be given instructions about undertaking an overnight fast. Subjects will bring their completed questionnaires to the first study visit.

Day -1. Arrive at Diabetes Clinic ([name]) from 7am-9am in fasted state.

Hand in completed records and questionnaires, which will be checked for completeness by the researchers. Any outstanding issues with the consent forms will be completed prior to venesection. A

fasting blood sample will be taken and anthropomorphic measurements will also be done in the fasting state. Subjects will be offered a light breakfast, as required and any outstanding paperwork will then be completed.

It is anticipated that up to 10 subjects will be screened on any given morning.

Day 0. Arrive at Canterbury University (College of Education Exercise laboratory, [name]) between 7am-10am either fasting or after a light breakfast (subject’s preference). Complete Maximal Treadmill Test.

Facilities and staff are available to undertake testing in up to twelve subjects per morning.

Days 2-14. Rest – await results of randomisation and group allocation.

Days 2-14 Start the exercise programme within a fortnight of randomisation.

**Exit interview for early termination of the study**

Subjects who elect to finish the programme early will be asked to undertake a (voluntary) exit interview, to better understand their likes and dislikes of the programme.

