#### A3. Study design

| A3.1 Describe the study design. Where this space is inadequate, continue on a separate sheet of paper. *Do not* delete page breaks or renumber pages. | |
| --- | --- |
|  | The study follows a randomised controlled trial (RCT) design and is divided into two Phases. Phase 1 is primarily an efficacy study, conducted over 12 weeks. This study will examine three exercise prescriptions (LIIT, MVIT, HIIT). Phase 2 is an effectiveness study, will be weighted towards Maori participation and will be conducted over 6 months. The exercise prescriptions used in Phase 2 will be the most successful high prescription from Phase 1 (ie either MVIT or HIIT), compared to a standard low intensity walking programme (LIIT) .The exercise prescription for the LIIT, MVIT and HIIT will be isocaloric ie those taking part in the high intensity arm of the programme will spend less overall time undertaking their exercise programme. Participants will have an elevated BMI and will not be regular exercisers. Participants will be asked to follow an exercise prescription as part of the study but will not be asked to change their diet. Participants must be physically well enough to able to undertake walking as their main form of exercise. Each phase will have separate participants.  All three of the exercise interventions will have a walking based component. They will be conducted by exercise leaders, trained to undertake the relevant exercise programmes in a standardised manner. (These exercise leaders will be provided by CPIT and are likely to include applied exercise physiology students undertaken a supervised Practicum). The exact intensity of exercise will however be individualised ie based on the subject’s pre-study fitness levels and performance when undertaking maximal volitional exercise. Fitness will improve during the study, thus exercise load will increase as the study progresses. Some subjects in the high intensity arm may therefore be considered ‘fit’ enough to incorporate a light jogging component to their exercise plan.  Data collection for Phase 1 will be undertaken before and after the twelve week intervention period. The same data will be collected for Phase 2 but will be collected at three time points: week 0, week 13 and week 26. Data will include a standardised exercise/fitness assessment, measuring V02 max on a treadmill test, standard anthropomorphic measurements, including waist circumference and an impedance measurement of total body fat, fasting venous blood collection for measurement of insulin, glucose, lipids and HsCRP. Subjects will complete several validated questionnaires including a four day food diary (to assess the extent that change in diet might act as a confounder) and quality of life assessments. The exercise physiology researchers undertaking the primary outcome measurement (VO2 max), will be blinded to group allocation.  Trial conduct, including the reporting of subject enrolment and follow up, will be undertaken using the CONSORT (Consolidated Standards of Reporting Trials) framework.  In summary phase 1 will look to use the positive results found in laboratory based heavily structured and tightly monitored exercise interventions and transfer these positive results to more community-based, less structured but still tightly controlled exercise intervention. In Phase 2 of the study we want to use the results found in phase 1 and apply them to an even less-structured, less tightly controlled but more realistic and much less expensive community-based exercise intervention.  (see Appendix 1 on separate sheet for more detail). |

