
#### A4. Participants

| A4.1 How many participants do you intend to recruit? (Include details for each locality organisation.) | |
| --- | --- |
|  | Phase 1;- 60 participants, anticipating that 48 will complete the study (16 in each arm).  Phase 2;- This less structured community based phase of the study is likely to experience a higher ‘drop out’ rate. 60 participants will be recruited, anticipating that 44 participants will complete the study (22 in each arm). |
|  | |
| A4.2 Give a justification for the number of research participants proposed, giving the details of power calculations when appropriate. | |
|  | A sample size of 16 in each group for the first study, will enable effect sizes >1.0 to be detected as statistically significant (two tailed-alpha=0.05) with 80% power. Assuming an untrained VO2 max of 30 ± 4ml/kg/min, this equates to differences in changes in VO2 max over 12 weeks of approximately 4 ml/kg/min.  A sample size of 22 per group in the second study will enable effect sizes >0.9 to be detected as statistically significant (two tailed-alpha=0.05) with 80% power, this equates to differences in changes in VO2max over 26 weeks of approximately 3.5ml/kg/min.  (To place this in context, a sedentary individual typically has a VO2 max of 25-35ml/kg/min +/- SD of 4 and a trained adult has a VO2 max around 40-60 ml/kg/min). |
|  | |
| A4.3 If randomisation is used, explain how this will be done. | |
|  | After consenting and baseline measurements, subjects will be randomly allocated in a 1:1:1 ratio to the exercise interventions, under the supervision of the medical biostatistician (CF).For both studies it is important to achieve a balance in gender and this will be achieved by stratified randomisation. |
|  | |

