#### A5. Statistical method

| A5.1 Is the method of analysis quantitative? | | | X | Yes |  | No |
| --- | --- | --- | --- | --- | --- | --- |
|  | | | | | | |
| Or qualitative? | | |  | Yes | X | No |
|  | | | | | | |
| If the method of analysis is **wholly qualitative**, go to question A5.4. If the method of analysis is **wholly or partly quantitative**, complete the following: | | | | | | |
|  | | | | | | |
| A5.2 Describe the statistical method that will be used to analyse the data. | | | | | | |
|  | Initial data analysis will be conducted by [name] and colleagues using the Statistical Package for the Social Sciences (SPSS) software programme. Final data analysis will be undertaken under the supervision of Associate [name], medical biostatistician. For both studies changes in continuous outcome measures (e.g. VO2max, BMI, etc) will be compared between groups using ANCOVA. These models will utilise the stratification variable, gender, as a factor and the baseline measure as a covariate. The appropriateness of these parametric analyses will be confirmed by visual inspection of the residual plots. If these do not confirm normality, data maybe transformed prior to analyses and if this does not remedy problems then non-parametric analyses will be undertaken. A two-tailed p value of <0.05 will be taken to indicate statistical significance.  The primary outcome measure is change in VO2max.  The secondary outcome measures are changes in: BMI, waist circumference, blood pressure, insulin sensitivity (HOMA) and lipids.  Tertiary outcome measures are changes in: % body fat as measured by bioimpedance, Quality of Life, hs CRP.  Samples will also be collected for an exploratory study measuring changes in a novel marker of muscular ‘fitness’, namely monocyte mitochondrial load. | | | | | |
|  | | | | | | |
| A5.3 Has specialist statistical advice been obtained about this study? | | | X | Yes |  | No |
|  | | | | | | |
| If **yes**, from whom? (A brief statistical report should be included if appropriate.) | | Associate [name], University of Otago. | | | | |
|  | | | | | | |
| A5.4 If the method of analysis is **wholly or partly qualitative**, specify the method. Why is this method appropriate? If interviews are to be used, include the general areas around which they will be based and a copy of the interview guide, if one is to be used. Copies of any questionnaires that will be used must be included. | | | | | | |
|  | Not applicable | | | | | |

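### No end-of-phase VO2max is stated for participants who stop exercising, although the protocol expects to lose 20% in Phase 1 and 26.7% in Phase 2

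*Protocol*

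**What the plan says.** **People who stop early.** Appendix 1, under its heading on early termination, says: "Subjects who elect to finish the programme early will be asked to undertake a (voluntary) exit interview". The stated purpose is to learn what they thought of the programme. No VO2max test, blood sample or body measurement is mentioned for them, and none is ruled out. Section B14 lets health professionals end an individual's involvement with the study on medical grounds. It does not distinguish that from ending the exercise alone.

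**Expected loss.** Section A4.1 recruits 60 per phase and expects 48 (16 per arm) and 44 (22 per arm) to complete. For Phase 2 it adds: "This less structured community based phase of the study is likely to experience a higher ‘drop out’ rate".

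**Power.** Section A4.2 uses the completer numbers. Sixteen per group "will enable effect sizes >1.0 to be detected as statistically significant (two tailed-alpha=0.05) with 80% power"; for Phase 2, "A sample size of 22 per group in the second study will enable effect sizes >0.9 to be detected as statistically significant", equated to about 3.5 ml/kg/min over 26 weeks.

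**Analysis.** Under section A5.2, changes in continuous outcomes "will be compared between groups using ANCOVA", with gender as a factor and baseline as a covariate. No analysis set and no method for missing outcomes is named.

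**Phase 2 visits.** Section A3.1 says that the data "will be collected at three time points: week 0, week 13 and week 26". The only use that Appendix 1 gives for the week-13 VO2max is checking progress and resetting training intensity.

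**The concern.** A VO2max that was never measured cannot be recovered by a later analysis plan, so this is a matter of data collection and has to be settled before enrolment.

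Adherence is part of the trial's rationale: the lay summary and section A2.2 suggest that shorter, harder sessions may be easier to keep up. Dropout may therefore differ by arm and be related to response. If only those who kept going are tested, the comparison tells us about people who kept going. Section A1.1 presents Phase 2 as mainly a study of effectiveness, where the question is what offering the programme achieves in everyone allocated to it.

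Phase 1 is described as mainly an efficacy study, so the point weighs less there. Even so, Phase 1 decides which high-intensity programme goes forward, and unequal loss between HIIT and MVIT could affect that choice.

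**Working it through.** **1. The protocol's own sample sizes.** Inputs from A4.2: two-sided alpha 0.05, power 80%, SD 4 ("Assuming an untrained VO2 max of 30 ± 4ml/kg/min"). The Phase 1 target is "differences in changes in VO2 max over 12 weeks of approximately 4 ml/kg/min", so d = 4/4 = 1.0. The Phase 2 target is 3.5, so d = 3.5/4 = 0.875, which the protocol rounds to 0.9.

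n per arm = 2(1.960 + 0.842)²/d²

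- Phase 1, d = 1.0: 15.7, so 16. The t-test gives 16.7, and power at 16 is 78.1%.
- Phase 2, d = 0.875: 20.5, so 21. The t-test gives 21.5, so 22.

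The stated 16 and 22 are reproduced to within one participant per arm.

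**2. Expected loss.** Phase 1: (60 − 48)/60 = 20.0%. Phase 2: (60 − 44)/60 = 26.7%. The inflation is arithmetically right: 48/0.8 = 60 and 44/(1 − 16/60) = 60.

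**3. What reaches the model.** ANCOVA of change needs a baseline and an end-of-phase value. With no end-of-phase test for stoppers, the expected input is 48 and 44 people, the same numbers used for power.

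**4. How far a completer difference can lie from the all-randomised difference in Phase 2.** The 3.5 comes from A4.2. The rest is assumed and not in the documents: low-intensity completers gain 2 ml/kg/min, high-intensity completers gain 2 + 3.5 = 5.5, and dropouts in both arms gain 0. With dropout shares p_HI and p_LI:

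difference = (1 − p_HI) × 5.5 − (1 − p_LI) × 2

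| Dropout, high v low intensity | Calculation | Difference |
|---|---|---|
| 40% v 13.3% | 0.600 × 5.5 − 0.867 × 2 | 1.57 |
| 26.7% v 26.7% | 0.733 × 5.5 − 0.733 × 2 | 2.57 |
| 13.3% v 40% | 0.867 × 5.5 − 0.600 × 2 | 3.57 |

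With 30 per arm, each row loses 16 of 60 in total. The completer figure is 3.5 throughout.

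**5. Power if everyone randomised were measured** (t-test, SD unchanged, 20 and 30 per arm).

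| Effect in stoppers (assumed) | Phase 1 | Phase 2 |
|---|---|---|
| Full | d = 1.0: 86.9% | d = 0.9: 92.9% |
| Half | d = 0.90: 79.2% | d = 0.78: 84.4% |
| None | d = 0.80: 69.3% | d = 0.66: 71.0% |

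**6. How many are randomised in Phase 2.** A4.1 recruits 60. Appendix 1 randomises 44, 22 per group. Form A gives 104 in total, which is 60 + 44, and section F2.1 also counts from 44. If 44 are randomised and 26.7% are lost, 44 × 44/60 = 32 remain, about 16 per group. Power at d = 0.9 is then about 69–70%.

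**The case against.** Four objections deserve an answer.

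- **Nothing prescribes a completer analysis.** A5.2 names no analysis set, and sizing on expected completers is an ordinary dropout allowance. This stands. A reader might infer that the protocol orders a completer analysis, but it does not. Analysis sets and missing-data methods are commonly left to the analysis plan, which is not shown, so their absence here is no fault.
- **Testing of stoppers is not forbidden.** Appendix 1 says that all Phase 1 subjects have paired tests, and the post-test schedules are not limited to adherers. This stands in part. That text is the general schedule; the exit section is the specific provision for stoppers and offers no test. The general line does not clearly override it.
- **Week-13 data are not excluded.** A reader might infer that week-13 results from later dropouts are discarded. The documents do not say so; they are silent on how the visits are modelled.
- **Bias need not flatter high intensity.** The protocol's rationale suggests better adherence with shorter sessions, which points to the 13.3% v 40% row. There the all-randomised difference is 3.57 against 3.5, so almost nothing changes. This stands, and it means that 1.6 cannot be quoted alone.

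**Conclusion.** The point holds as a gap in outcome collection. The protocol expects 20% loss in Phase 1 and 26.7% of those recruited in Phase 2, and the only procedure it gives for people who stop is a voluntary interview. On that text, the ANCOVA of change would rest on those who were tested.

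The 26.7% should not be read as a share of those randomised, because the documents disagree on whether 60 or 44 are randomised in Phase 2.

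The size and direction of any bias are unknown. The range of about 1.6 to 3.6 ml/kg/min against 3.5 depends on the assumed gains and on which arm loses more. It shows that the completer difference can be well away from the all-randomised one or nearly equal to it. It does not show that the effect would be overstated. The matter is most serious for Phase 2, given its effectiveness aim and higher expected loss.

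**What to change.** **Exit section, Appendix 1.** Separate stopping the exercise programme from withdrawing from the study. State that participants who stop, still consent and are judged medically fit to test are invited to the scheduled VO2max, blood and anthropometry visits: the end of the 12 weeks in Phase 1, and weeks 13 and 26 in Phase 2. Keep the interview as an addition.

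**Section A5.2.** State that all randomised participants with outcome data are analysed in their allocated arm. For Phase 2, a repeated-measures model over weeks 13 and 26 (baseline, gender, arm by time), with the week-26 contrast as primary, is preferable, so that week-13 data from later dropouts contribute. A completer analysis can be secondary.

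**Phase 2 numbers.** Reconcile A4.1, Appendix 1, F2.1 and Form A on how many are recruited and how many randomised.

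**Cost.** Mainly wording. Section B1 already schedules these visits for participants, and E9 already provides petrol vouchers for them. Some stoppers will decline. The estimated effect may be smaller than in completers, and if stoppers show no group difference, power would be about 69% and 71%. The sponsor should know this before enrolment starts.

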**Post Testing (after 12 weeks)**

Follow the same schedule as above for the baseline testing ie fasting venesection etc at Diabetes Centre, followed the next day by measurement of VO2 max.

**Variables to be Measured**

*Questionnaires.* The following validated questionnaires will be used:

*Fasting venous blood collection*

1. Insulin

2. Fasting glucose

3. Insulin sensitivity (HOMA %)

4. B-cell function (HOMA %)

5. Blood lipid profile (HDL, LDL, VLDL, triglycerides)

6. Highly sensitive C-reactive protein

7. DNA collection, for storage for mitochondrial depletion studies

*Anthropometric Measurements*

1. Height, weight, waist and hip circumferences.

2. Bio-impedance measurement (Fat free mass, fat mass, % body fat)

*Physiological Measurements before, during and after VO2max Test*

1. Resting: HR, BP, SV, Q (Finapres Finometer)

2. During Exercise: HR, VO2, RER, VE Perceived exertion.

3. Post-exercise: Perceived exertion, HR

*Physiological Measurements before, during and after Submax Test*

1. Resting: HR, BP, SV, Q (Finapres Finometer)

2. During Exercise: HR, BP, SV, Q, VO2, RER, VE

3. Post-exercise: HR, BP, SV, Q, VO2, RER, VE

From the VO2max test we will calculate the VO2peak, time to exhaustion, HRpeak while from the submaximal test we will calculate workload efficiency and cardiovascular stress at 50% of VO2peak.

**Phase 2.**

The subjects will be randomly selected to one of 2 groups (Low intensity control group and High-intensity intervention group). The exercise prescription for these two groups will be based on the outcomes from phase 1 of the study and will be for 26 weeks rather than twelve weeks. The measurement of V02 max, fasting blood samples, questionnaires and anthropomorphic measurements will be as for Phase 1, but undertaken at 0, 13 and 26 weeks. Mitochondrial depletion studies will not be undertaken for Phase 2 (ie they will be done for Phase 1 only). The only location that will change is the location for the exercise prescription, which will now be near the subjects’ own home ie around the Aranui or Halswell area.
